#### **4.2.3 Downloading Site Registration Documents**

Download the site registration forms from the protocol-specific page located on the CTSU members' website. Permission to view and download this protocol and its supporting

documents is restricted to institutions and their associated investigators and staff on a participating roster. To view/download site registration forms:

- Log on to the CTSU members' website (<https://www.ctsuo.org>);
- Click on *Protocols* in the upper left of your screen
  - Enter the protocol number in the search field at the top of the protocol tree, or
  - Click on the By Lead Organization folder to expand, then select *Alliance*, and protocol number *A022104*;
- Click on *Documents, Protocol Related Documents*, and use the *Document Type* filter and select *Site Registration* to download and complete the forms provided. (Note: For sites under the CIRB initiative, IRB data will load automatically to the CTSU as described above).

#### **4.2.4 Submitting regulatory documents**

Submit required forms and documents to the CTSU Regulatory Office using the Regulatory Submission Portal on the CTSU members' website.

To access the Regulatory Submission Portal log in to the CTSU members' website, go to the *Regulatory* section and select *Regulatory Submission*.

Institutions with patients waiting that are unable to use the Regulatory Submission Portal should alert the CTSU Regulatory Office immediately by phone or email: [name], or [contact] to receive further instruction and support.

#### **4.2.5 Checking site registration status**

Site registration status may be verified on the CTSU members' website.

- Click on *Regulatory* at the top of the screen;
- Click on *Site Registration*; and
- Enter the site's 5-character CTEP Institution Code and click on Go.
  - Additional filters are available to sort by Protocol, Registration Status, Protocol Status, and/or IRB Type.

Note: The status shown only reflects institutional compliance with site registration requirements as outlined within the protocol. It does not reflect compliance with protocol requirements for individuals participating on the protocol or the enrolling investigator's status with NCI or their affiliated networks.

### **4.3 Patient Registration Requirements**

#### **4.3.1 Informed consent**

The patient must be aware of the neoplastic nature of his/her disease and willingly consent after being informed of the procedure to be followed, the experimental nature of the therapy, alternatives, potential benefits, side-effects, risks, and discomforts. Current human protection committee approval of this protocol and a consent form is required prior to patient consent and registration.

Patients with impaired decision making capacity may be enrolled on this study, where institutional policy and IRB of record allow.

#### 4.4 Patient registration/randomization procedures (Step 1)

The Oncology Patient Enrollment Network (OPEN) is a web-based registration system available on a 24/7 basis. OPEN is integrated with CTSU regulatory and roster data and with the LPOs' registration/randomization systems or the Theradex Interactive Web Response System (IWRS) for retrieval of patient registration/randomization assignment. OPEN will populate the patient enrollment data in NCI's clinical data management system, Medidata Rave.

Requirements for OPEN access:

- Active CTEP registration with the credentials necessary to access secure NCI/CTSU IT systems;
- To perform enrollments or request slot reservations: Must be on an LPO roster, ETCTN Corresponding roster, or participating organization roster with the role of Registrar. Registrars must hold a minimum of an Associate Plus (AP) registration type;
- If a Delegation of Tasks Log (DTL) is required for the study, the registrars must hold the OPEN Registrar task on the DTL for the site; and
- Have an approved site registration for the protocol prior to patient enrollment.

To assign an Investigator (IVR) or Non-Physician Investigator (NPIVR) as the treating, crediting, consenting, drug shipment (IVR only), or receiving investigator for a patient transfer in OPEN, the IVR or NPIVR must list the IRB number used on the site's IRB approval on their Form FDA 1572 in RCR. If a DTL is required for the study, the IVR or NPIVR must be assigned the appropriate OPEN-related tasks on the DTL.

Prior to accessing OPEN, site staff should verify the following:

- Patient has met all eligibility criteria within the protocol stated timeframes; and
- All patients have signed an appropriate consent form and Health Insurance Portability and Accountability Act (HIPAA) authorization form (if applicable).

**Note:** The OPEN system will provide the site with a printable confirmation of registration and treatment information. You may print this confirmation for your records.

Access OPEN at <https://open.ctsu.org> or from the OPEN link on the CTSU members' website. Further instructional information is in the OPEN section of the CTSU website at <https://www.ctsu.org> or <https://open.ctsu.org>. For any additional questions, contact the CTSU Help Desk at [name] or [[contact]](mailto:[contact]).

#### 4.5 Stratification Factors and Treatment Assignments

The randomization routine is found in Section 13 (Statistical Considerations).

##### 4.5.1 Stratification Factors

- 1) Tumor stage based on clinical evaluation: T4 vs. T1-3
- 2) Nodal stage based on clinical evaluation: N+ vs. N0
- 3) The distance from the lower edge of tumor to the anal verge: 0 to < 4cm;  $\geq 4$ cm to < 8cm;  $\geq 8$ cm to  $\leq 12$ cm

##### 4.5.2 Treatment Assignments

The factors defined in Section 4.5.1 will be used as stratification factors.

After the patient has been registered into the study, the values of the stratification factors will be recorded, and the patient will be assigned to one of the following treatment groups using the Pocock and Simon dynamic allocation procedure which balances the marginal distributions of the stratification factors between the treatment groups.

- 1) LCRT followed by mFOLFOX6 (or CAPOX)
- 2) LCRT followed by mFOLFIRINOX

## 5.0 STUDY CALENDAR

Laboratory and clinical parameters during treatment are to be followed using individual institutional guidelines and the best clinical judgment of the responsible physician. It is expected that patients on this study will be cared for by physicians experienced in the treatment and supportive care of patients on this trial.

### Pre-study Testing Intervals

The pre-study testing intervals are guidelines only. When calculating days of tests and measurements, the day a test or measurement is done is considered Day 0. Therefore, if a test were done on a Monday, the Monday one week later would be considered Day 7.

**To be completed  $\leq$  28 DAYS before registration:** All laboratory studies, history and physical.

**To be completed  $\leq$  42 DAYS before registration:** Any X-ray, scan of any type or ultrasound which is utilized for tumor measurement per protocol.

**To be completed  $\leq$  60 DAYS before registration:** Any baseline exams used for screening, or any X-ray, scan of any type or ultrasound of uninvolved organs which is not utilized for tumor measurement.

## ARM 1

| Evaluations during treatment – Arm 1 (LCRT THEN FOLFOX OR LCRT THEN CAPOX) |     |                 |    |    |    |    |    |    |    |                    |
|----------------------------------------------------------------------------|-----|-----------------|----|----|----|----|----|----|----|--------------------|
| Study Week (+/- 14 days)*                                                  | Pre | 10  | 12 | 14 | 16 | 18 | 20 | 22 | 24 | 32-38  |
| History and physical**                                                     | X   | X               | X  | X  | X  | X  | X  | X  | X  | X                  |
| Height                                                                     | X   |                 |    |    |    |    |    |    |    |                    |
| Adverse Event Assessment                                                   | X   | X               | X  | X  | X  | X  | X  | X  | X  | X                  |
| Colorectal surgeon eval                                                    | X   | X               |    |    |    |    |    |    |    | X                  |
| Med Onc                                                        | X   | X               | X  | X  | X  | X  | X  | X  | X  | X                  |
| Rad Onc                                                                    | X   | X               |    |    |    |    |    |    |    |                    |
| DRE (digital rectal exam)                                                  | X   | X               |    |    |    |    |    |    |    | X                  |
| Sigmoidoscopy/
Proctosigmoidoscopy***                                   | X   | X               |    |    |    |    |    |    |    | X                  |
| Biopsy                                                         | X   |                 |    |    |    |    |    |    |    |                    |
| MRI Rectum                                                                 | X   |                 |    |    |    |    |    |    |    | X                  |
| CT CAP                                                         | X   |                 |    |    |    |    |    |    |    | X                  |
| CBC & diff                                                     | X   |                 |    |    |    |    |    |    |    |                    |
| CMP & CEA                                                                  | X   | X               |    |    |    |    |    |    |    | X                  |
| Pregnancy Test****                                                         | X   |                 |    |    |    |    |    |    |    |                    |

**ARM 2**

| Evaluations during treatment – Arm 2 (LCRT THEN mFOLFIRINOX) |     |                 |    |    |    |    |    |    |    |                    |
|---------------------------------------------------------------------|-----|-----------------|----|----|----|----|----|----|----|--------------------|
| Study Week (+/- 14 days)*                                           | Pre | 10  | 12 | 14 | 16 | 18 | 20 | 22 | 24 | 32-38  |
| History and physical**                                              | X   | X               | X  | X  | X  | X  | X  | X  | X  | X                  |
| Height                                                              | X   |                 |    |    |    |    |    |    |    |                    |
| Adverse Event Assessment                                            | X   | X               | X  | X  | X  | X  | X  | X  | X  | X                  |
| Colorectal surgeon eval                                             | X   | X               |    |    |    |    |    |    |    | X                  |
| Med Onc                                                 | X   | X               | X  | X  | X  | X  | X  | X  | X  | X                  |
| Rad Onc                                                             | X   | X               |    |    |    |    |    |    |    |                    |
| DRE(digital rectal exam)                                            | X   | X               |    |    |    |    |    |    |    | X                  |
| Sigmoidoscopy/
Proctosigmoidoscopy***                            | X   | X               |    |    |    |    |    |    |    | X                  |
| Biopsy                                                  | X   |                 |    |    |    |    |    |    |    |                    |
| MRI Rectum                                                          | X   |                 |    |    |    |    |    |    |    | X                  |
| CT CAP                                                  | X   |                 |    |    |    |    |    |    |    | X                  |
| CBC & diff                                              | X   |                 |    |    |    |    |    |    |    |                    |
| CMP & CEA                                                           | X   | X               |    |    |    |    |    |    |    | X                  |
| Pregnancy Test****                                                  | X   |                 |    |    |    |    |    |    |    |                    |

\* Timing can vary based on institutional standards (for example, if a center waits longer than 14 days between starting chemotherapy after completion of LCRT this is not a protocol violation) as some centers wait 4-6 weeks after LCRT completion to start systemic chemotherapy. As such, exact week number from registration may vary and as such can be adjusted to reflect timing of start of chemotherapy.

\*\* Weight, Pulse, BP. Performance Status will only be required at pre, week 10 and weeks 32-38.

\*\*\* Should be completed by the evaluating/treating surgeon for baseline evaluation and during treatment assessments to maintain continuity of the response assessment (as this is critical for the primary endpoint). Baseline characteristics that should be captured include distance from the anal verge, photos, and the percent circumference of the lumen involved by the tumor. If the surgeon evaluating the patient at baseline completed the colonoscopy that was diagnostic then this would be sufficient for the initial baseline endoscopic evaluation as long as the baseline characteristics of the tumor were captured including distance from the anal verge, photos and baseline characteristics of the tumor (as above). Given the importance for the primary endpoint it is critical for a surgeon to be involved who is willing to evaluate the primary tumor for the endpoint throughout the duration of the trial. The surgeon involved should be affiliated with an NCTN hospital or hospital system. It is permissible for the evaluating surgeon to be at a separate institution from the treating medical and radiation oncology teams as long as there is continuity in the management and seamless sharing of relevant clinical data between the teams (assuming all teams are part of NCTN or NCTN-affiliated hospitals and the arrangement is convenient for the patient). Further, the evaluating surgeon must have access to the protocol, all relevant documents and the tumor response forms to participate.

\*\*\*\* For women of childbearing potential (see Section 3.2.3). Must be done ≤ 7 days prior to registration.

 Time of evaluation dependent on duration of neoadjuvant chemotherapy FOLFOX (16 weeks) or CAPOX (15 weeks)

 8-12 weeks (+/- 4 weeks) after completion of all neoadjuvant therapy

 Patients will be seen and evaluated during neoadjuvant chemoradiation and chemotherapy with necessary laboratory evaluations per institutional guidelines. For neoadjuvant chemotherapy, recommendation is to be evaluated by medical oncology during (Arm 1) and (Arm 2) chemotherapy every two weeks (every three weeks for patients getting CAPOX) or as needed per institutional guidelines. In patients not seen and evaluated by medical oncology every cycle, adverse events must still be collected and reported every cycle by relevant research staff.

 Biopsy to confirm pathological diagnosis of rectal adenocarcinoma is REQUIRED

 CT of the Chest, Abdomen and Pelvis. Prefer with intravenous contrast, but per institutional standards based on patient's labs and medical condition.

 CBC & diff, CMP performed at baseline and with each cycle of chemotherapy or per institutional standards.

 Assessment by surgeon, medical and radiation oncology occurs in a multidisciplinary fashion to ensure the patient has tolerated LCRT well and does not have to occur exactly at week 10; simply should occur prior to initiation of chemotherapy and is meant to ensure appropriate transition to the medical oncology team as they begin systemic chemotherapy.

**Evaluations during follow-up for WW patients (after completion of TNT with cCR and post-TNT restaging)**

| Years on study                                | Year 1
(Every 3 months) |   |   |    | Year 2
(Every 3 months) |    |    |    | Year 3
(Every 6 months) |    | Years 4-5**
(Every 6 months) |    |    |    |
|-----------------------------------------------|----------------------------|---|---|----|----------------------------|----|----|----|----------------------------|----|---------------------------------|----|----|----|
| Months after post-TNT restaging (+/- 30 days) | 3                          | 6 | 9 | 12 | 15                         | 18 | 21 | 24 | 30                         | 36 | 42                              | 48 | 54 | 60 |
| History and Physical                          | X                          | X | X | X  | X                          | X  | X  | X  | X                          | X  | X                               | X  | X  | X  |
| Sigmoidoscopy/
Proctosigmoidoscopy         | X                          | X | X | X  | X                          | X  | X  | X  | X                          | X  | X                               | X  | X  | X  |
| MRI Rectum                                    |                            | X |   | X  |                            | X  |    | X  |                            | X  |                                 | X  |    | X  |
| CT CAP                            |                            |   |   | X  |                            |    |    | X  |                            | X  |                                 | X  |    | X  |
| CEA levels                        | X                          | X |   | X  | X                          | X  |    | X  | X                          | X  | X                               | X  | X  | X  |

\*If TME completed via abdominoperineal resection – not relevant and unnecessary

\*\*MRI in years 4 through 8 would only be supported if clinically indicated by treating team.

 CT of the Chest, Abdomen and Pelvis Patients in the TME group will be followed according to NCCN guidelines.[1]

 After 36 months, CEA will be evaluated every 6 months up to five years, based on NCCN guidelines.

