### 7.3 Surgery

All patients will undergo assessment at 8-12 weeks post-TNT completion. If patients have a cCR (no tumor on endoscopy, MRI, or clinical exam using the MSK regression schema) then patients may be offered a WW approach or TME depending on the outcome of a thorough discussion with their treating physician concerning the risks and benefits of each approach and both they and their physician agree with the intended approach. If the patients have an incomplete response (any evidence of residual tumor by endoscopy, MRI or clinical exam using the MSK regression schema) then they be recommended to undergo TME (not mandated and identical to OPRA). Of note, and as in OPRA, if patients have a near complete response (nCR) then patients can undergo a repeat assessment 8 weeks later (+/-2 weeks). If there is any evidence that the tumor has stopped responding, persists or regrows then the patient will be recommended to undergo TME (e.g. nCR that fails to evolve to a cCR at 20 weeks (+/- 4 weeks) post-completion of TNT OR local regrowth after initial cCR determination). If there is a discrepancy between MRI and endoscopy/DRE then endoscopy/DRE should take precedence in the decision making on whether to proceed to WW or TME.

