## 12.0 END OF TREATMENT/INTERVENTION

### 12.1 Duration of Protocol Treatment

During neoadjuvant treatment, protocol treatment (intervention) is to continue until completion of LCRT and 8 cycles of consolidation chemotherapy, distant disease progression, local/regional disease progression which precludes surgery, or unacceptable adverse events. After neoadjuvant treatment, TME will be performed when it is appropriate (incomplete response to assigned TNT regimen (e.g. residual tumor remains, no evolution to complete response). Please see the study calendar (Section 5) and the treatment section (Section 7) for treatment and follow-up time periods.

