## 12.3 Follow-up

### 12.3.1 Duration of Follow- up (Please see study calendar in section 5.0 for complete list of follow-up tests and procedures)

|                                                                                                                                              | MRI rectum                                                                                                     | Endoscopy and digital rectal exam                                   | CT chest, abdomen, pelvis                                                   | CEA                                                                                         |
|----------------------------------------------------------------------------------------------------------------------------------------------|----------------------------------------------------------------------------------------------------------------|---------------------------------------------------------------------|-----------------------------------------------------------------------------|---------------------------------------------------------------------------------------------|
| All patients who completed pre-operative protocol treatment                                                                                  | Pre-treatment, post-TNT re-staging                                                                             | Pre-treatment, post-TNT re-staging                                  | Pre-treatment, Post-TNT re-staging, annually from 5 years post-registration | Pre-treatment, every 3-6 months post-TNT in Years 1-2, every 6 months post-TNT in Years 3-5 |
| All patients who are off pre-operative protocol treatment early due to Progression of disease-                                               | As per treatment team                                                                                          | As per treatment team                                               | As per treatment team                                                       | As per treatment team                                                                       |

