## 13.0 STATISTICAL CONSIDERATIONS

### 13.1 Study Endpoints

#### 13.1.1 Primary Endpoints:

- **Phase II:** The primary endpoint is cCR rate. The cCR rate is defined as the number of patients who achieved cCR at the end of TNT divided by number of patients included in the analysis population (see Section 13.4.1). This endpoint will be assessed within 8-12 weeks after completion of TNT. If there is a cCR, then the patient will be counted in the numerator. If there is a near-complete response (nCR) then a re-evaluation within 4-8 weeks will be performed. If the tumor has evolved to a cCR, then the patient will be counted in the numerator. Otherwise, the patient will be deemed as NOT achieving cCR status.
- **Phase III:** Disease-free survival (DFS): is defined as the time from date of randomization to the date of first occurrence of the following events:
  - Death due to all causes
  - Tumor that recurs locally after an R0 TME
  - Tumor that regrows after an initial apparent clinical and radiological CR and cannot be surgically removed with an R0 TME\*
  - M1 disease diagnosed at any point after the initiation of treatment

\* Regrowth for patients who are on watch and wait approach (regardless of treatment assignment) that can be surgically removed with an R0 TME will NOT be a DFS event

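### The re-evaluation that settles phase II cCR for near-complete responders is mandatory at 4-8 weeks in 13.1.1, optional at 8 ± 2 weeks in 7.3, and on no Section 5.0 calendar

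*Combined protocol and SAP*

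**What the plan says.** **Endpoint definition (13.1.1).** After the first post-TNT assessment, "If there is a near-complete response (nCR) then a re-evaluation within 4-8 weeks will be performed". A patient who has become cCR by then enters the numerator. For everyone else the rule is "Otherwise, the patient will be deemed as NOT achieving cCR status".

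**Treatment section (7.0 and 7.3).** Section 7.0 lists a second assessment after 8 weeks as one of three management routes, beside watch and wait (WW) and surgery. Section 7.3 says that "if patients have a near complete response (nCR) then patients can undergo a repeat assessment 8 weeks later (+/-2 weeks". It then recommends TME where there is an "nCR that fails to evolve to a cCR at 20 weeks (+/- 4 weeks) post-completion of TNT".

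**Calendars (5.0).** The Arm 1 and Arm 2 calendars end in a single restaging column at weeks 32-38, which footnote 2 places 8-12 weeks (± 4 weeks) after neoadjuvant therapy. The WW calendar is titled "Evaluations during follow-up for WW patients (after completion of TNT with cCR and post-TNT restaging", so it is for patients already in cCR. The TME calendar begins after resection. None has a row, column or footnote for an nCR re-evaluation.

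**Follow-up table (12.3.1).** For patients who completed treatment, the MRI and the endoscopy/DRE cells read "Pre-treatment, post-TNT re-staging". The WW row then gives routine surveillance intervals. No row shown has an nCR visit.

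**Cross-references.** Section 12.3.1 says "Please see study calendar in section 5.0 for complete list of follow-up tests and procedures". Section 12.1 says "Please see the study calendar (Section 5) and the treatment section (Section 7) for treatment and follow-up time periods". Section 11.2 also refers to Section 5.0 for the schedule.

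**The concern.** For an nCR patient the phase II primary endpoint depends on one visit. The section that governs analysis requires that visit; the section that governs care only permits it, in a different window; and the calendars that sites are told to follow do not list it.

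Two things can go wrong for a site acting in good faith. It can follow 7.3 and leave the visit out for a patient who defers surgery. Or it can hold the visit at 8-10 weeks and find a cCR after the 13.1.1 window has closed, where the plan does not say whether that cCR counts. Either way a true converter can be scored as a non-responder. Because 13.1.1 gives the same default score to a failed re-evaluation and to one that never took place, the endpoint alone would not tell them apart.

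The same status also defines who enters the one-year regrowth monitoring population in 13.5.1 (patients in cCR who chose WW), so a misscored converter could be missing there as well.

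**Working it through.** **1. The plan's own phase II figure.** Inputs from 13.3.1: 148 per arm, cCR 50% against 67%, one-sided alpha 0.048.

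- Pooled rate = (0.50 + 0.67)/2 = 0.585. Null SE = √(2 × 0.585 × 0.415/148) = 0.0573.
- Alternative SE = √((0.50 × 0.50 + 0.67 × 0.33)/148) = 0.0564.
- Power = Φ((0.17 − 1.665 × 0.0573)/0.0564) = 0.907, against the stated 90.5%.

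The figure reproduces. The point concerns how the endpoint is ascertained, not the sample size.

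**2. The two windows, in days after restaging.**

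| Source | Rule | Days |
|---|---|---|
| 13.1.1 | 4-8 weeks | 28-56 |
| 7.3 | 8 ± 2 weeks | 42-70 |
| Both satisfied | | 42-56 |
| 7.3 only | | 57-70 |
| 13.1.1 only | | 28-41 |

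The 7.3 window has 70 − 42 + 1 = 29 days, of which 70 − 56 = 14 lie outside the endpoint window. The 7.3 target, 8 weeks = day 56, is the last day that 13.1.1 allows.

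**3. Can a scheduled visit stand in?** The first WW visit is month 3 ± 30 days: 3 × 30.44 ± 30 = about days 61-121. It does not overlap days 28-56, touches 7.3 only at about days 61-70, has no MRI (first at month 6), and belongs to patients already in cCR. It cannot replace the re-evaluation. The ± 4 weeks in calendar footnote 2 is the tolerance of the single restaging visit, not a second visit.

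**4. Weeks after TNT.**

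| | Restaging 8-12 weeks | Restaging 4-16 weeks (footnote 2, ± 4) |
|---|---|---|
| Re-evaluation per 7.3 (+6 to +10) | 14-22 | 10-26 |
| Re-evaluation per 13.1.1 (+4 to +8) | 12-20 | 8-24 |

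The 7.3 decision point is 20 ± 4 = 16-24 weeks. It constrains the second look loosely and does not remove the mismatch in step 2.

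**5. How an nCR patient is scored under 13.1.1.**

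| Path | Score |
|---|---|
| Direct TME | Not cCR |
| Re-evaluated days 28-56, converted | cCR |
| Re-evaluated days 28-56, not converted | Not cCR |
| Re-evaluated days 57-70, converted | Not stated; outside the window as written |
| TME deferred, not re-evaluated | Not cCR |

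**6. Scale per patient.** One converter scored as a non-responder lowers that arm's rate by 1/148 = 0.68 points at the final analysis (threshold 9.3 points) and by 1/74 = 1.35 points at the interim (futility below 1.2 points). If a share L of cCRs were lost equally in both arms, the assumed 17-point difference would become 17 × (1 − L) points, which costs some power. The documents give no nCR, conversion or omission rate, so L cannot be filled in.

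**The case against.** The best reply is that the visit is already provided for. Section 13.1.1 is protocol text and is mandatory; 7.0 names the route; 7.3 gives a window and an action rule that a site cannot apply without looking again; 11.2 names endoscopy, MRI and DRE as the modalities before a TME decision; and 12.1 sends sites to Section 7 as well as Section 5. The permissive verb in 7.3 has an innocent reading: it lets an nCR patient wait instead of going to surgery. The specimen schedule in 6.2 speaks of a first re-staging, which suggests that more than one is expected. The 12.3.1 table as extracted shows no TME row, so rows may be missing. The response forms, training video and Data Submission Schedule, where the visit may be put into operation, are not in the documents.

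Much of this stands. It is why most sites will probably do the re-evaluation, and why it would be wrong to say that the protocol makes no provision for it. It does not remove the conflict. Neither 7.0 nor 7.3 requires the visit or its MRI, and the window mismatch remains even if every site performs it. Section 13.4.2 waits for cCR status on all treated patients before the final analysis, but the default in 13.1.1 supplies a status without a visit.

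A reader might go further and infer bias between the arms, since treatment is open-label. The documents do not support that: both arms have the same restaging column, 7.3 applies to both, and no mechanism for a differential is shown. Nor does the interim arithmetic show that the futility decision is fragile for this reason. At 37 against 37 responders p = 0.50 (stop), and at 38 against 37 p = 0.435 (continue), but any single misclassified patient at a boundary does the same.

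**Conclusion.** The conflict is real and should be corrected. For nCR patients, 13.1.1 and 7.3 differ on whether the endpoint-deciding visit is required and on when it falls. Their windows share only days 42-56, and the visit is on no Section 5.0 calendar and in none of the 12.3.1 rows shown.

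The consequence is limited to possible misscoring of true converters as non-responders, at 0.68 points per patient at the final analysis and 1.35 at the interim. The total size and direction cannot be determined. Omission at equal rates in both arms would mainly cost some power. The phase III DFS definition does not use cCR status as an event.

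This rests on reading both windows from the restaging date, on the 12.3.1 rows as extracted, and on the documents alone. If the Data Submission Schedule or response forms already require the visit, the practical risk is smaller, but the two texts still need to agree.

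**What to change.** 1. **13.1.1:** use one re-evaluation window that covers both texts, for example 4-10 weeks after restaging with a target of 8 weeks, and state that a cCR found within it counts. Visits compliant with either section then remain valid. Narrowing to 8 ± 2 weeks would instead exclude, or need an exception for, the 4-6 week visits that 13.1.1 now allows. Give the same window and target in 7.0 and 7.3.
2. **7.3:** state that nCR patients who do not go directly to TME must have the re-evaluation, with endoscopy, DRE, MRI rectum and the tumor response assessment form. Direct TME stays available and is scored not cCR, as now.
3. **5.0 and 12.3.1:** add a conditional nCR re-evaluation column or footnote to both arms' calendars and a matching table entry.

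The wording should be settled without reference to cCR results by arm. The cost is a slightly wider endpoint window and an occasional MRI that might otherwise have been skipped. Sample size and decision thresholds do not change.
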